#### Exclusion criteria

v Middle age adolescence who are sick

v Middle age adolescence who are practicing in weight management

v Middle age adolescence whose sibling or relatives studying in other schools will be selected for the study

v Middle age adolescence who is below 50th percentile or underweight

#### 3.7.3 Sampling technique

Probability stratified random sampling technique will be used for this study. In stratified random sampling, the strata are formed based on individuals' shared attributes or characteristics. Simple random sampling technique (lottery method) will be used to select 3 schools from Arakonam, Vellore District. From the above population 150 samples will be selected from 3 Higher Secondary Schools. 50 samples will be selected from each school. Each class as 5-6 divisions consisting of 45-50 students in each section. One section from each class is randomly selected 15-20 samples who fulfilled the inclusion criteria will be taken as a sample from the particular class. Thus, 150 students are selected from class 10, 11 and 12th standards.

#### 3.7.4 Sample size

Sample size was calculated by Power analysis based on the Pilot study.

#### 3.8 Development of tool

The investigator used the following steps for preparation of the tools for the study

- Extensive literature review

- Preparation of the blue print for the tools

- Consultation with experts from the field of study

- Preparation of the final draft of the tools

- Editing of the tools

#### 3.9 Description of the tools

**Part I:** Questionnaire to assess demographic characteristics of the middle age adolescents. It includes age in years, gender, order of born, type of family, education, religion, locality of residence, monthly income of parents (in rupees), occupation of father and mother, educational status of father and mother, family history, and source of information on Atherosclerosis.

**Part II:** Checklist to assess the prevalence of Atherosclerosis in middle age adolescents

**Part III:** A structured questionnaire to assess knowledge on prevention of Atherosclerotic risk factors among middle age adolescents

**Part IV:** Adolescent physical activity questionnaire (APAQ) to assess physical activity among middle age adolescence for last 7 days

[figure not shown]

Part V: Adolescent Food Habit Checklist (AFHC) to assess the food habits among middle age adolescence

Part VI: Adolescent Sedentary Activity Questionnaire (ASAQ) to assess the sedentary activity among middle age adolescence for weekdays and weekends

3.10 Score Interpretation

Part I

The information on demographic data to be collected from the middle age adolescence on 15 variables and this was not scored but it is used for descriptive analysis.

Part II

These tools included; general appearance of the subjects, anthropometric measurement, and bio-physiological measurements. For Anthropometric measurements, the cut off value for height, weight, BMI and waist circumference will be calculated as per standard recommended by Indian Academy of Pediatrics (Revised IAP Growth Charts for Height, Weight, BMI and Waist circumference for 5 to 18 years old Indian Children). The blood pressure will be assessed on centile values of Indian standard (IAP).

1. Scoring for Height in cm and Weight in Kg for boys and girls

- < 25 Percentile - Below normal
- 50th Percentile - Normal
- 75th Percentile - Normal
- 90th Percentile - Below abnormal (action point to prevent obesity)
- 97th Percentile - Abnormal

2. Scoring cut off value for BMI for boys and girls

The following formula use to calculate Body Mass Index (BMI)

$$BMI = \text{Weight (kg)} / \text{Height (m}^2\text{)}$$

- < 25th percentile - Underweight
- 50th Percentile - Normal
- 75th percentile - Normal
- 85th Percentile - Overweight (action point to prevent obesity)
- 95th percentile - Obese

3. Scoring cut off value for Waist Circumference for boys and girls

- < 25th percentile - Underweight
- 50th Percentile - Normal
- 75th percentile - Overweight (action point to prevent obesity)

[figure not shown]

95th percentile - Obese

Scoring for Bio - Physical measurements

4. Scoring cut off value for systolic pressure and diastolic pressure for boys and girls

< 25th percentile - Hypotension

50th Percentile - Normal

75th percentile - Pre hypertension (action point to prevent hypertension)

95th percentile - Hypertension

Part III

It consists of 40 items. Each question had three answers with only one correct answer. When the response is correct 'one' mark was given and for the wrong answer 'zero'. The knowledge covered areas like general information of atherosclerosis, risk factors, symptoms, diagnosis and prevention of risk factors.

Scoring for Knowledge

| Sl.No.       | Areas of Knowledge         | No. of Items |  | Score     |
|--------------|----------------------------|--------------|--|-----------|
| 1            | General Information        | 9            |  |           |
| 2            | Risk factors               | 10           |  |           |
| 3            | Symptoms                   | 8            |  |           |
| 4            | Diagnosis                  | 3            |  |           |
| 5            | Prevention of risk factors | 10           |  |           |
| Total |                            | 40    |  | 40 |

SCORING

Total item = 40, Total score 40 = 100%

<20 items: <50% Inadequate Knowledge

21 – 30 items: 51 – 75% Moderate Knowledge

>31 items: - >75% Adequate Knowledge

[figure not shown]

Part IV: Physical Activity Questionnaire among Middle Age Adolescence (Kowalski et al., 2004)

SCORING

1) Item 1 (Spare time activity)

- Take the mean of all activities ("no" activity being a 1, "7 times or more" being a 5) on the activity checklist to form a composite score for item 1.

2) Item 2 to 7 (PE, lunch, right after school, evening, weekends, describes you best)

- The answers for each item start from the lowest activity response and progress to the highest activity response

- Simply use the reported value that is checked off for each item (the lowest activity response being a 1 and the highest activity response being a 5).

3) Item 8

- Take the mean of all days of the week ("none" being a 1, "very often" being a 5) to form a composite score for item 8.

4) Item 9

- Can be used to identify students who had unusual activity during the previous week, but this question is **NOT** used as part of the summary activity score. As a researcher will refer the subjects to the health centers with the stakeholders.

5) How to calculate the final PAQ-A activity summary score

- Once you have a value from 1 to 5 for each of the 8 items (items 1 to 8) used in the physical activity composite score, you simply take the mean of these 8 items, which results in the final PAQ - A activity summary score.

A score of 1 indicates low physical activity, whereas a score of 5 indicates high physical activity.

Part V: Food Habit Questionnaire among Middle Age Adolescence (Johnson et al., 2002)

SCORING

1 point for each 'healthy' response. Final score should be adjusted for 'not applicable' and missing responses using the formula: AFHC score = no of 'healthy' responses x (20/no of items completed).

Part VI: Sedentary Activity Questionnaire among Middle Age Adolescence (Hardy et al., 2007)

SCORING

Time spent in each category of sedentary behavior.

Total time being sedentary will be calculated for weekdays, weekend days and all days.

The values then characterized as poor, fair, and good practice.

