### 1.5 Operational Definitions

**Effectiveness:** It refers to the outcome in the knowledge, physical activity, sedentary activity, and dietary pattern score after structured interventional strategy, daily physical activity, reduction screen time, and changes in healthier dietary pattern by structured and modified standardized questionnaire.

**Structured interventional strategy:** It refers to written and verbal materials used for teaching with assistance of video, which is prepared by the researcher. It is intended to provide information on knowledge, physical activity, sedentary activity, and dietary pattern regarding atherosclerosis and its prevention among middle age adolescence.

**Knowledge:** It refers to the written responses of the middle age adolescence regarding prevention of atherosclerotic risk factors measured by a structured questionnaire prepared by the researcher which includes general information, risk factors, symptoms, diagnosis, and prevention. The score '1' is given for right answer and '0' given for wrong answer. The total score is '40'. The composite score for knowledge will be calculated by adding the scores for all domains and rescaling it within 100. Scores will then be recoded into three categories: Inadequate knowledge: score considered < 50%; moderately adequate knowledge: score considered 51 - 75%; adequate knowledge: score considered 76 - 100%.

**Physical activity:** It refers to physical exercise done by middle age adolescents measured by modified standardized physical activity questionnaire. It consists of 8-items value from 1 to 5 for each item (Items 1 to 8) used in the physical activity composite score, simply take the mean of these 8 items, which results in the final PAQ - A activity summary score. A score of '1' indicates low physical activity, whereas a score of '5' indicates high physical activity (Kowalski et al., 2005).

**Dietary pattern:** It refers to food habits of middle age adolescents measured by modified standardized adolescent food habit checklist (AFHC). It consists of 20-items, 1 point for each 'healthy' response. Final score should be adjusted for 'not applicable' and missing responses using the formula: AFHC score = no of 'healthy' responses x (20/no of items completed) (Johnson et al., 2002).

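### The knowledge bands give a score of 20 out of 40 no category and contradict themselves at 31, and the percentile lists do not fix a student's BMI category or separate height from an obesity label (minor).

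*Protocol*

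**What the plan says.** **Knowledge.** Section 3.10, Part III, gives one mark per item, with "Total item = 40, Total score 40 = 100" per cent. It then sets three lines that pair an item count with a percentage: "<20 items: <50% Inadequate Knowledge", "21 – 30 items: 51 – 75% Moderate Knowledge" and ">31 items: - >75% Adequate Knowledge". Section 1.5 rescales the score to 100 and says it will be recoded into three categories: "Inadequate knowledge: score considered < 50%; moderately adequate knowledge: score considered 51 - 75" per cent, and adequate from 76 to 100 per cent.

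**Percentile lists.** Section 3.10, Part II, takes its cut-offs from the IAP growth charts. For BMI it labels values under the 25th percentile as underweight and then names single percentiles: the 50th and 75th as normal, "85th Percentile - Overweight (action point to prevent obesity"), and the 95th as obese. The waist and blood pressure lists have the same form.

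**Height.** One list is headed "Scoring for Height in cm and Weight in Kg for boys and girls". In it, the 90th percentile carries an action point to prevent obesity and the 97th is called abnormal.

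**The concern.** Bands used to recode a score should place every attainable value in exactly one category. Here one knowledge score has no category, and another has two answers depending on which half of a line is followed. The score of 20 lies on the boundary between inadequate and moderate knowledge, where a change of category from pre-test to post-test would be counted.

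The percentile lists have a related fault. A list of single percentiles does not say whether each one opens or closes a category. Objective 1 in section 1.3.2 is the prevalence of atherosclerotic risk factors, and section 1.5 says this is measured partly by anthropometry. Two analysts with the same data could therefore report different prevalences of overweight and obesity. Placing height on a list with an obesity label also lets stature alone attract that label.

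**Working it through.** **Knowledge: inputs.** There are 40 items at one mark each (section 3.10). The domain counts reproduce the total: 9 + 10 + 8 + 3 + 10 = 40. One item is therefore 100/40 = 2.5 per cent.

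**Classification.** All 41 possible scores (0 to 40) were classified under three rules: the item counts in 3.10, the percentages in 3.10 and the percentages in 1.5. The scores around the two boundaries are:

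| Score | Per cent | Item count, 3.10 | Per cent, 3.10 | Per cent, 1.5 |
|---|---|---|---|---|
| 19 | 47.5 | inadequate | inadequate | inadequate |
| 20 | 50.0 | none | none | none |
| 21 | 52.5 | moderate | moderate | moderate |
| 30 | 75.0 | moderate | moderate | moderate |
| 31 | 77.5 | none | adequate | adequate |
| 32 | 80.0 | adequate | adequate | adequate |

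The other 39 scores receive the same single category under all three rules. The percentage bands of 1.5 and 3.10 agree at every attainable score, so the contradiction at 31 is between the item count and the percentages.

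**How many students.** The protocol gives no score distribution for this questionnaire. The literature review (section 2) cites an Indian school study with mean 41.1 (SD 10.5) before and 48.1 (SD 16.9) after teaching, out of 100. Assume that these carry over and that scores are roughly normal. Multiplying by 0.4 gives 16.44 (SD 4.20) before and 19.24 (SD 6.76) after. The chance of score k is Φ((k + 0.5 − mean)/SD) − Φ((k − 0.5 − mean)/SD).

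- Score 20, pre-test: Φ(0.967) − Φ(0.729) = 0.066; × 150 = 9.9 students.
- Score 20, post-test: Φ(0.186) − Φ(0.038) = 0.059; × 150 = 8.8 students.
- Score 31, post-test: Φ(1.814) − Φ(1.666) = 0.013; × 150 = 2.0 students. At pre-test it is practically none.

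To show the dependence on this assumption, keep SD 4.20 and move the mean. With the mean at 20, the chance of scoring 20 is Φ(0.119) − Φ(−0.119) = 0.095, or 14 of 150. With the mean at the guessing level for three-option items (40/3 = 13.3), it is Φ(1.706) − Φ(1.468) = 0.027, or 4 of 150.

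**BMI list.** The single percentiles can be read in two natural ways:

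| Percentile range | Named value opens the category | Named value closes the category |
|---|---|---|
| 25th to 50th | none | normal |
| 50th to 75th | normal | normal |
| 75th to 85th | normal | overweight |
| 85th to 95th | overweight | obese |
| above 95th | obese | none |

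Eligibility requires BMI above the 50th percentile (section 3.7.2), so the disagreement from the 75th to the 95th falls among enrolled students. The hole from the 25th to the 50th lies outside baseline eligibility. It would matter only at screening, or for a student who falls below the 50th at follow-up.

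**Height.** No arithmetic is needed: height and weight share one list, and its 90th-percentile label refers to obesity.

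**The case against.** The case for leaving this alone has several parts.

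- **Score 31.** It is adequate by the percentage on its own line and by section 1.5, so the fault may be one mistyped inequality. That is fair. It is missed by item count only and should not be counted as having no category anywhere. Score 20 has no such rescue.
- **The magnitude is borrowed.** It comes from another instrument with six domains, in pupils aged 14 to 16. This stands, so the counts only illustrate scale.
- **Unequal loss before and after.** A reader might infer that pre-post comparisons are distorted because different numbers drop out at each test. The borrowed figures do not show it: 9.9 against 8.8 at score 20, or 9.9 against about 10.7 with score 31 added, is about one student in 150 either way.
- **Fixed shares of students without a BMI category or wrongly flagged on height.** A reader might try to put percentages on these. Any such figure depends on choosing one reading of lists that allow several, and the BMI and height lists would have to be read the same way. No rule in the protocol counts a tall student as having an adiposity risk factor; section 1.5 lists overweight or obesity, not stature. What stands is that the list puts an obesity label on a height percentile.
- **The categories are not the main result.** Section 1.5 defines effectiveness through scores and provides a 0 to 100 composite. Knowledge is not among the primary or secondary outcomes in section 1.6, and nothing says that BMI will be analysed in categories. This stands and limits the severity.

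The objection does not remove the point. Section 1.5 commits to recoding knowledge into three categories, and the protocol itself sets the cut-offs.

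**Conclusion.** The point holds as a minor defect. Followed literally, the knowledge key leaves a score of 20 unclassified in both sections and contradicts itself at 31. These two results follow from the protocol's own figures and rest on no assumption. The counts do rest on one: if the cited study's scores carried over under a normal approximation, about 9 to 10 of 150 students per visit would score 20 (4 to 14 under the shifted means shown), and about 2 would score 31 at post-test.

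The BMI list is ambiguous between the 75th and 95th percentiles, within the enrolled range, so the overweight and obesity prevalence under objective 1 depends on the reader. Height should not share a list that carries an obesity label.

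The effect stops at categorised knowledge and risk-factor prevalence summaries. A reader might go further and doubt the BMI outcome or the trial's size. The documents do not support that: the sample size and any continuous analysis of BMI or of the knowledge score do not use these bands.

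**What to change.** 1. **Knowledge.** State one set of contiguous bands, worded identically in sections 1.5 and 3.10, and assign 20 explicitly. For example, 0–20, 21–30 and 31–40 would classify all 41 scores and agree with the stated percentages at every score other than 20, where the protocol currently gives none.
2. **Percentile lists.** Rewrite each list in 3.10, Part II, as contiguous ranges that show which end is included, and reconcile them with the IAP standard the section already cites. This calls for no new cut-offs.
3. **Height.** Separate height from the list carrying the obesity action label, so that stature alone is not labelled an obesity marker.

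The cost is an edit to the scoring key and to section 1.5, best made before baseline. If item scores and raw measurements are kept, data already collected can be re-banded.

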3.11 Conclusion

A high prevalence of cardiovascular disease risk factors and their disproportional distribution among the study population indicated an inevitable risk of cardiovascular events in near future.

Increased awareness and improved primary care services may decrease the incidence of coronary artery disease and improve overall quality of life (Ahmed et al., 2017). Overweight, excess body fat, lipid profile, sedentary behavior, and history of CVD in family were the most prevalent cardiovascular risk factors among adolescents. The adolescents had higher rates of overweight and excess fat. As for the stages, a higher percentage of individuals with sedentary behavior, overweight, total cholesterol and LDL in comparison with other stages. Individuals with changes in nutritional status were more likely to develop hypertension, changes in total cholesterol, LDL, triglycerides, insulin, and low HDL when compared to healthy individuals. Concluded that the cardiovascular risk factors have been observed in younger and younger individuals and are important factors to identify a population at risk (do Prado et al., 2015). Cardiovascular risk factors are highly prevalent among school children. Importantly, school children lack adequate knowledge regarding cardiovascular risk factors. School based interventions are required for cardiovascular risk reduction in childhood.

[figure not shown]

